**For phase II:**

For the trial phase of the study, the aim is to assess the effect of co-administration with fatty foods, and of dual-dose versus single-dose albendazole on hookworm cure rate. The cure rate of single dose albendazole for hookworms varies between 36% and 93% in previously reported studies. Based on data from Adegnika et al (42), we power our trial to detect a difference in cure rate of 70% versus 50% for both co-administration with fatty foods versus no co-administration, and for dual-dose versus single-dose albendazole.

With type I error probability of 5%, 93 participants in each comparison group will be required for 80% power to detect a difference in cure rate of 70% versus 50%. Therefore, the total target sample size for the trial will be 186. However, allowing for 5% loss to follow-up, i.e. 5% of hookworm positive cases not appearing on the follow up stool test 21 days after treatment, the target sample size will increase to 196. If the expecting prevalence of hookworm in 2021 is 12%, to satisfy the sample size of 196, the target sample size of the prevalence survey of 2021 will be 1,634. Therefore, a total sample size of 1,650 will be sufficient to cover sample size requirements of both the prevalence survey and the nested trial.

Assuming that 50 children will be selected from each school, a total of 33 schools will be randomly selected in order to achieve the required sample size.

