The cure rate of anthelminthic drugs against STH decreases when faecal egg count is high at pre-treatment (22). But, it is also known that the fecundity of residual female hookworm increases after treatment, caused by the relaxation of adult hookworm density(23,24). It means that the faecal egg count reduction test (FECRT) can reveal a wide range of drug efficacy against STHs within different human STHs cases. Kotze and Kopp suggested exclusion of cases with the heaviest infections from a FECRT to improve the interpretation of FECRT as an indicator of drug efficacy(24).

- - - 1. **Lack of absorbing albendazole and increasing albendazole absorption with fatty meal**

When it comes to albendazole absorption in the intestine, research has shown that albendazole absorption increases five to six-fold if taken with a fatty meal (25,26). Ceballo *et al*. assessed the serum pharmacokinetics of albendazole and its metabolites in eight Argentine adults. They showed a high variation of serum concentration of albendazole sulphoxide (ABZSX) among participants, which can be one reason why people show different cure rates when taking the same dose of albendazole (27). Therefore, it is necessary to consider and evaluate approaches for increasing albendazole absorption in order to improve drug efficacy against human hookworm, since individuals have different albendazole absorption.

In previous studies done in a range of countries; Brazil, Cameroon, Cambodia, China, Ethiopia, India, Lao PDR, Tanzania, and Vietnam, the cure rate of single-dose albendazole for hookworm ranged from 36 to 93%(22,28–30). According to the study done in Gabon by Adegnika *et al*., the cure rate of double-dose albendazole for hookworm was 92%; on the other hands, the cure rate of single-dose albendazole was 54% (31).

Avocado is one of the easily accessible foods containing high fat in rural areas of Uganda. 100 g of avocado contains 15g of fat, 2g of protein, and 8.5g of carbohydrate (32).

- - - 1. **Albendazole dissolution**

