**Faecal egg counts from hookworm positive**

**stool samples**

**Albendazole**

**Dual-dose treatment with avocado (n=53)**

**Albendazole**

**Dual-dose without avocado treatment (n=53)**

**Albendazole**

**Single-dose treatment with avocado**

**(n=53)**

**Albendazole**

**Single-dose treatment without avocado (n=53)**

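### The 80% power stated for the avocado comparison rests on a 50% no-avocado cure rate that the cited source trial does not support: half of those children get the dual dose, and on that source the expected rate is 73%

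*Protocol*

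**What the plan says.** The trial is a 2x2 factorial (section 3.2) with equal allocation to four arms (section 3.4). The comparison without avocado therefore contains the single-dose control arm and, in equal number, the arm shown in Fig 1 as "Dual-dose without avocado treatment (n=53" children.

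Section 3.6.1, under the phase II heading, names the Gabon trial as the basis and states "we power our trial to detect a difference in cure rate of 70% versus 50% for both co-administration with fatty foods versus no co-administration". It applies the same pair of rates to the dose comparison. On the number needed it says: "With type I error probability of 5%, 93 participants in each comparison group will be required for 80% power". The total is 186, raised to 196 for 5% loss to follow-up. The same paragraph notes: "The cure rate of single dose albendazole for hookworms varies between 36% and 93% in previously reported studies".

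The Introduction, in the part on albendazole absorption with a fatty meal, reports the Gabon trial: "the cure rate of double-dose albendazole for hookworm was 92%; on the other hands, the cure rate of single-dose albendazole was 54" per cent. It quotes no avocado or fatty-meal cure rate from that trial. The protocol gives no assumed cure rate for any of the four arms, and no assumption on how the two interventions combine.

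**The concern.** One pair of rates, 70% versus 50%, is used for two different questions. For dose, a source is quoted and 20 points is a cautious reading of its 38-point difference. For avocado, nothing quoted supports the 20 points. The 50% reference looks like the rate of a single arm (single dose, no avocado) used as the rate of a pooled group, half of which receives the better-performing dose in the cited trial.

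The direction matters. If dual dose cures about 92%, there is little room for avocado to improve on it, and the pooled avocado difference is diluted. Avocado is objective i in section 2.2. A non-significant result there would be judged against a stated 80% power whose cited basis does not support it, and one shared figure hides how differently the two questions may be powered.

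**Working it through.** **Inputs.** Type I error 5% (two-sided is inferred, since it reproduces the printed n), 80% power, 70% v 50%, 93 per side and 5% loss, all from section 3.6.1. Source cure rates of 54% and 92%, from the Introduction. Equal allocation, from section 3.4. Any avocado effect below is an assumption.

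**Step 1: reproduce the plan.** With P the mean of p1 and p2,

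n per side = [1.96 × √(2P(1−P)) + 0.8416 × √(p1(1−p1) + p2(1−p2))]² / (p2−p1)².

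For 50% v 70%: (1.96 × 0.6928 + 0.8416 × 0.6782)² / 0.04 = 1.9287² / 0.04 = 93.0. Then 2 × 93 = 186, and 186/0.95 = 195.8, so 196. All three figures reproduce.

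**Step 2: what the stated margins imply for the arms.** Let a = single dose without avocado, b = single with avocado, c = dual without avocado, d = dual with avocado, in per cent. Requiring 50 v 70 on both factors gives a + c = 100, b + d = 140, a + b = 100 and c + d = 140. Hence b = c = 100 − a and d = 40 + a.

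- a = 40 gives 40/60/60/80. This is coherent, and both comparisons have 80% power.
- a = 54, the quoted single-dose rate, gives 54/46/46/94. Dual dose alone would have to cure 46%, against 92% in the source.

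**Step 3: the no-avocado side on the cited data.** (54 + 92)/2 = 73%. No avocado assumption enters here.

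**Step 4: avocado power from a 73% reference.** Power = Φ{[(p2−p1)√n − 1.96√(2P(1−P))] / √(p1(1−p1) + p2(1−p2))} with n = 93. For 73% v 83%: (0.10 × 9.644 − 1.96 × 0.5858) / 0.5815 = −0.316, so power is 37.6%.

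| Assumed avocado effect | Cells a/b/c/d (%) | Avocado margins (%) | Avocado power | Dose power | n per side for 80% (avocado) |
|---|---|---|---|---|---|
| 54 to 70 on single dose only | 54/70/92/92 | 73 v 81 | 25% | >99% | 434 |
| +20 on single dose only | 54/74/92/92 | 73 v 83 | 38% | >99% | 269 |
| Odds ratio 2.33 (70 v 50) at both doses | 54/73.3/92/96.4 | 73 v 84.8 | 51% | >99% | 186 |
| +20 on single dose, dual dose at 100% | 54/74/92/100 | 73 v 87 | 67% | >99% | 127 |
| Avocado as good as a second dose | 54/92/92/92 | 73 v 92 | 93% | 93% | 62 |

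**Step 5: what 80% takes.** From 73%, a marginal gain of 16 points (73 v 89) gives 79.9%. The marginal gain is the average of the gains at the two doses, so this means about 54 to 78 on single dose if dual dose rises to 100%, or about 54 to 86 if dual dose is unchanged.

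**Sensitivity.** Stratifying by dose raises rows 2, 3 and 4 to about 42%, 57% and 75%. Taking the 53 per arm of Fig 1, less 5% loss (100.7 per side), gives 40%, 54% and 70% unstratified. None of these reaches 80%.

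**The case against.** There is no arithmetic fault. The sample size reproduces, and applying a two-group formula to the margins of a factorial trial is ordinary practice. The stated margins are coherent: 40/60/60/80 satisfies them exactly, and 40% on single dose lies inside the 36% to 93% range quoted in the same paragraph. A power statement names a difference worth detecting and need not forecast four arms. The protocol also stresses that cure rates vary by country and by albendazole brand, so it need not expect 54% in Mayuge.

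A large avocado effect cannot be excluded either. The Introduction reports a five- to six-fold rise in absorption with a fatty meal, and if avocado matched a second dose, power would be 93%. Stratified analysis, finally, is something a statistical analysis plan could settle.

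Most of this stands. A reader might infer that the formula is wrong for this design, or that the source figures by themselves put avocado power at 38% to 67%. The documents support neither. The source has no avocado result, so that range also needs an assumed 20 points on single dose and 0 to 8 on dual dose.

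What the objection does not remove is the claimed basis. Section 3.6.1 ties 70% v 50% for both factors to a trial whose quoted rates put the no-avocado side at 73% and say nothing about avocado. The cells that would justify 50% are never stated.

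**Conclusion.** The concern holds as a fault in the input rates and their sourcing, not in the formula or in N. On the protocol's quoted source the no-avocado side is expected at 73%, so the stated 80% power for avocado is not supported by its cited basis.

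The size is conditional. With 54% and 92% without avocado, and avocado adding 20 points on single dose, power is 38% to 67% (51% with a common odds ratio of 2.33), while dose power exceeds 99%. Over other avocado effects it runs from about 25% to 93%. These figures assume a two-sided 5% test of the pooled comparison with 93 evaluable per side.

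A reader might go further and conclude that the avocado comparison is certainly underpowered. The documents do not support that: the range straddles 80%, and a marginal gain of about 16 points would reach it.

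**What to change.** Keep N = 196. In section 3.6.1:

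- State the assumed cure rate of each of the four arms, and label the avocado effect as an assumption.
- Derive the dose and avocado margins from those rates, and give power separately for each factor. Show the range over plausible avocado effects, not one value.
- Remove the statement that 70% v 50% for avocado is based on the Gabon trial.

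Compare avocado with no avocado stratified by dose, for example by Mantel-Haenszel. This fits the design and recovers a few points of power (38% to about 42%, and 67% to about 75%, in the two bounding cases).

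The cost is a rewritten paragraph and one line of analysis, with no more children. The downside is a less favourable stated power for avocado.

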**Exclusion criteria are:**

1. Children who received praziquantel and albendazole within three months before the prevalence survey to avoid the residual effect of previously administrated drugs of praziquantel and albendazole.
2. Children who have a history of allergic reaction to either albendazole or praziquantel.
3. Children whose stool results come out as *Ascaris lubmricoides, Trichuris trichiura* ^[[1]](#footnote-1)^and other parasites infection apart from hookworm infection will not take part in the trial.

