**3.3.2 Selection of classes**

Within each selected school, a class (40-50 children) will be selected among the P4 and P5 classes (9-10-year-old schoolchildren) using a table of random numbers or a lottery method. If only one class of this age group is present that class has to be selected. If the number of children present in the selected class is lower than 35, a second class will be selected and all children in both classes examined.

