## 3.6 Sample size and sampling method

**3.6.1 Sample size**

**For phase I:**

Sample size determination for the prevalence survey will be based on the comparison of prevalence of schistosomiasis and soil-transmitted helminths in Mayuge district in 2019 with the anticipated prevalence of STH and schistosomiasis after two years’ project implementation.

The baseline prevalence of STHs in 2019 was 15.8 % and it is anticipated that MANE program activities will reduce the prevalence of STHs to 12% by the time of the 2021 survey. For schistosomiasis, the prevalence was 27.2% in 2019, and it is estimated that MANE program activities will reduce schistosomiasis prevalence to 18% by the time of the 2021 survey.

Applying to the difference of expecting prevalence of STH in 2021 and proven prevalence of STHs in 2019, a target sample size for the 2021 prevalence survey of 1300 participants would be required for 80% power to detect a difference between 2019 and 2021 STH prevalence at 5% significance level.

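### Screening 1,650 children is not shown to supply 196 trial participants: the margin is two children, with no allowance for the exclusion of other parasites

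*Protocol*

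**What the plan says.** All references are to the Protocol.

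- **Phase II sample size (3.6.1).** "With type I error probability of 5%, 93 participants in each comparison group will be required for 80% power to detect a difference" of 70% versus 50% in cure rate. That makes 186, and after allowing for "5% of hookworm positive cases not appearing on the follow up stool test 21 days after treatment, the target sample size will increase to 196". The 196 is divided by a 12% hookworm prevalence to give 1,634, which becomes 33 schools of 50 children. The section concludes that "a total sample size of 1,650 will be sufficient to cover sample size requirements of both the prevalence survey and the nested trial".
- **Phase I sample size (3.6.1).** For all soil-transmitted helminths (STH), "it is anticipated that MANE program activities will reduce the prevalence of STHs to 12% by the time of the 2021 survey". For schistosomiasis, the programme is expected to "reduce schistosomiasis prevalence to 18% by the time of the 2021 survey", from 27.2% in 2019.
- **Baseline survey (MANE project section).** Hookworm made up 170 of the 177 STH-positive samples.
- **Exclusion criteria (3.2), third item.** Children with Ascaris, Trichuris and "other parasites infection apart from hookworm infection will not take part in the trial".
- **Selection of classes (3.3.2).** One class of 40 to 50 children is taken per school. "If the number of children present in the selected class is lower than 35, a second class will be selected", and then all children in both classes are examined.
- **Figure 1 (3.2).** It shows 212 hookworm-positive children at 12% prevalence, in four arms of 53.
- **Fallback (end of 3.6.1).** If low hookworm prevalence leaves the trial short of 196, further children in high-prevalence schools are tested.

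**The concern.** The sufficiency statement fixes the number of schools and supports the stated 80% power. It treats every hookworm-positive child as a trial participant. The exclusion criteria do not, and the same survey examines for schistosomiasis, which the plan expects to be common. The 12% used for hookworm is also the figure that the phase I text gives for all STH, and 50 per school is the top of the class-size range in 3.3.2.

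If the yield is overstated, the purposive top-up becomes a likely source of participants instead of a contingency. Without it, the trial would have less power than stated.

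**Working it through.** **Reproducing the plan's figures.** The inputs are 50% v 70%, two-sided 5%, 80% power and no continuity correction. The protocol does not state sidedness; two-sided reproduces its figure.

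n per comparison group = [1.96·√(2·0.6·0.4) + 0.8416·√(0.5·0.5 + 0.7·0.3)]² / 0.20² = 93, so 186 in total. Then 186/0.95 = 195.8, so 196; 196/0.12 = 1,633.3, so 1,634; and 33 × 50 = 1,650. Every step reproduces.

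**Margin.** 1,650 × 0.12 = 198, two above target. The expected yield falls below 196 once just over 1% of positives are ineligible (1 − 196/198 = 1.0%).

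**Inputs for the corrected yield.**
- Hookworm prevalence: 12% as stated, or 0.12 × 170/177 = 11.53% if the STH forecast is scaled by the 2019 hookworm share.
- Share removed by the third exclusion: 0 if schistosomiasis does not count. If it counts, 18% (the 2021 forecast) or 27.2% (no change from 2019), assuming co-infection is independent of hookworm. The documents give no co-infection rate.
- Children screened: 1,650, or 33 × 45 = 1,485 with an assumed mean of 45 per school, the midpoint of 40 to 50.

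**Formulas.** Expected eligible = screened × prevalence × (1 − share removed). Analysed = 0.95 × eligible. With m = analysed/2 per comparison group, power = Φ{[0.20·√m − 1.96·√(2·0.6·0.4)] / √(0.5·0.5 + 0.7·0.3)}.

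| Screened | Hookworm | Removed | Eligible | Analysed | Power |
| --- | --- | --- | --- | --- | --- |
| 1,650 | 12% | 0 | 198.0 | 188.1 | 80.4% |
| 1,650 | 11.53% | 0 | 190.2 | 180.7 | 78.8% |
| 1,650 | 12% | 18% | 162.4 | 154.2 | 72.2% |
| 1,650 | 11.53% | 18% | 155.9 | 148.1 | 70.4% |
| 1,650 | 12% | 27.2% | 144.1 | 136.9 | 66.9% |
| 1,650 | 11.53% | 27.2% | 138.4 | 131.5 | 65.1% |
| 1,485 | 12% | 0 | 178.2 | 169.3 | 76.1% |
| 1,485 | 11.53% | 0 | 171.2 | 162.6 | 74.4% |
| 1,485 | 12% | 18% | 146.1 | 138.8 | 67.5% |
| 1,485 | 11.53% | 18% | 140.3 | 133.3 | 65.7% |

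**Screening needed for 196 eligible with 18% removed.** 196/(0.12 × 0.82) gives 1,992, and 196/(0.1153 × 0.82) gives 2,074. That is 40 to 42 schools at 50 children each.

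**Figure 1.** 12% of 1,650 is 198, not 212. To expect 212 positives, 212/0.12 = 1,767 children would have to be screened.

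**The case against.** The strongest reply is that nothing is miscalculated. The 1,634 is explicitly conditional on 12% hookworm, and 50 per school is openly an assumption. The inputs are forecasts, and forecasts can differ. This stands as far as it goes: the division is right, and the fault lies in what it leaves out.

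The prevalence point is minor. The phase II text gives 12% as its own hookworm assumption, 11.53% rounds to 12%, and the change from 198 to 190 costs about one to two points of power. It matters only because the margin is two children.

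On class size, a reader might infer that the plan needs 50 children in every class. It needs a mean of 50 per school, and schools where a second class is added can exceed 50. The 45 used above is an assumption.

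The exclusion drives most of the shortfall, and its size rests on two unknowns: whether schistosomiasis counts, and the rate of co-infection. The literal wording has no carve-out, so counting it is the natural reading, but it is not certain. Positive association with hookworm would remove more than 18%, and negative association less.

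Finally, the fallback keeps 196 as the target and can make up the number. That is correct, and it limits the consequence. However, its trigger names only low hookworm prevalence, not losses from exclusions or small classes, and a top-up does not make the statement about 1,650 true.

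**Conclusion.** The statement that 1,650 is sufficient for the trial does not hold on the protocol's own inputs. It leaves two children to spare and allows nothing for a criterion that, as worded, could remove a substantial share of positives.

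- **Schistosomiasis counts, and is independent of hookworm at 18%:** about 162 eligible, or 156 with the scaled prevalence. That is 34 to 40 short of 196, with power of about 72% or 70% unless topped up.
- **Schistosomiasis does not count:** about 190 to 198 at 50 per school, or about 171 to 178 at an assumed 45. Only the top of this range meets the target.

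Two stronger readings are tempting. One is that 140 to 162 children are simply to be expected. The documents do not support that as a flat forecast: the whole range needs schistosomiasis to count and independence to hold, and the low end also needs the assumed 45 per school. The other is that the trial is planned to end below 186 evaluable children. The fallback is written to restore 196, so the lower power figures apply only if it is not used. The survey half of the sufficiency sentence is not in question here.

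**What to change.** 1. Reconcile the third exclusion criterion in 3.2 with the sample-size section by stating which infections it covers, including whether schistosomiasis is among them. Which scope is intended is for the investigators to settle.
2. In 3.6.1, restate the expected yield and screening number using a hookworm prevalence, the share removed by that criterion (with its assumption stated) and the class size that 3.3.2 is likely to deliver. If schistosomiasis counts, the screening number is about 1,990 to 2,075 at the forecast rates.
3. Correct Figure 1: 12% of 1,650 is 198, not 212. Align the arm sizes with the target of 196.
4. Widen the fallback's trigger to any shortfall below 196, whatever the cause. Describe the top-up as likely to be needed, and state the power if it is not used.

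The cost is wording, a less favourable stated yield, and use of the top-up screening already provided for. No change to arms, outcomes or randomisation is needed.

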**The scenario of not having enough number of participants for the phase II trial:**

If the prevalence of hookworm in the survey is lower than anticipated so that the target sample size of 196 for the phase II trial is not achieved, the MANE team will purposely select hookworm high prevalence school(s) and test for hookworm among those who are not taking part in the phase I prevalence survey. For example, after the phase I prevalence survey, if twenty more participants will be needed, and the prevalence of hookworm in school “A” is 50%, the MANE team will additionally select approximately 40 students in school “A”.

## 3.7 Data management and analysis

Quality control is important to ensure quality outcome of the data. The following measures will be undertaken to secure the quality of this study.

- Completed questionnaires and written notes will be crosschecked immediately after exercise and during the nights of each successive fieldwork to ensure that each relevant question has been asked and the response properly recorded.
- Field workers for stool sample collection and interview will be comprehensively trained before data collection, drawing special attention to interviewing techniques, recording of responses, probing, ethics and data handling/management among others.
- The research instruments will be pre-tested and amended as necessary.
- Appropriate supervision of the entire data collection process will be ensured by the team leader and supervisors.
- Field diaries will be kept by the study team to record any events deemed important for the interpretation of the results.

**3.7.1 Data analysis**

The MANE team will use Open data kit (ODK) of World Vision for data generation, collection and store

1. ODK build: pre-tested questionnaire questions will be transferred into ODK format.
2. ODK collect: pre-trained field workers will collect data from the participants during the prevalence survey
3. ODK aggregate: collected data will be uploaded and stored into World Vision ODK server.

Data saved in the ODK system will be exported into Microsoft Office Excel, and the data will be checked errors, any missing values, and extreme values. The cleaned data will be exported to the statistic program (Stata or R).

Prevalence of STHs and schistosomiasis with 95% confidence intervals will be calculated. The arithmetic eggs count will be obtained from the microscopic examination of the Kato-Katz method applying made slide. A multiplication factor of 24 should be applied to calculate eggs per gram, since the stool quantity in a slide prepared with the Kato-Katz method contains 41.7mg of the stool. The intensity of infection will be categorised by the criteria of WHO guideline as below(13).

|  | Light intensity infections | Moderate intensity infections | Heavy intensity infections |
| --- | --- | --- | --- |
| *A. lumbricoides* | 1-4,999 epg | 5,000-49,999 epg | ≥ 50,000 epg |
| *T.trichiura* | 1-999 epg | 1,000-9,999 epg | ≥ 10,000 epg |
| Hookworm | 1-1,999 epg | 2,000-3,999 epg | ≥ 4,000 epg |
| *S.mansoni* | 1-99 epg | 100-399 epg | ≥ 400 epg |

(Table 2) The threshold of infection intensity by each STH and *S.mansoni*

I will analyse the relationship between the prevalence and the risk factors from the questionnaire survey. Chi-square (χ2) test or Fisher’s exact test will be applied to assess categorical variables on the prevalence of STHs and schistosomiasis. χ2 Test for trend will be used for evaluating ordered categorical variables on the prevalence of STHs and schistosomiasis. The univariate analysis will be carried out to identify the association between potential risk factors and prevalence. I will conduct multivariate logistic regression analysis to determine which risk factors are associated with the outcomes of the prevalence of STHs and schistosomiasis, with the risk factors significantly (p-value < 0.05) associated with hookworm and schistosomiasis infection.

Continuous variables such as eggs counts for the dependent variable will be assessed by using t-test.

When analysing the results of the trial of fatty meal co-administration with single-, and dual-dose albendazole, the primary outcomes will be cure rate and egg reduction rate among four different groups, Chi-square (χ2) test will be applied for analysing the difference of cure rate among four treatment groups. Differences in eggs count between enrolment and follow-up will be assessed by using paired t-test. Chi-square (χ2) test or Fisher’s exact test will be applied to assess categorical variables on the difference of cure rate with four different options of treatment against hookworm. χ2 Test for trend will be used to evaluate ordered categorical variables on the difference of cure rate with four different treatment options against hookworm.

- - **Precautionary measures for the prevalence survey in the context of COVID-19**.

The WHO published the interim guideline of conducting a variety of NTDs related activities in the context of COVID-19 in the name of considerations for implementing mass treatment, active case finding and population-based surveys for neglected tropical diseases in the context of COVID-19 pandemic: interim guidance(43). According to this guideline, for conducting prevalence survey safely during the COVID-19 pandemic situation, there must be following precautionary measures as indicated in the WHO guideline. There are considerations how to take precautionary measures applicable to designated sites for planned activities (table 3 in the interim guidance), precautionary measures for health staff and community health workers (table 4 in the interim guidance), and precautionary measures for the target population(table 5 in the interim guidance).

1. Dissemination Plan

This survey will be conducted with multiple stakeholders including the ministry of health of Uganda, donor organisation (KOICA), scientists from academic partners (London School of Hygiene and Tropical Medicine), policymakers, and health professionals. The results will be written and made academic transcripts for dragging attention to reducing the NTDs burden in Uganda. The results will not reflect any personal information.

Therefore, when the study is complete, the study team will compile and analyse the data, and the overall results will be shared with the study participants and their parents/guardians. The research findings will be disseminated to the Ugandan authorities, donor organisation, policymakers, scientists, and the general public through a variety of forms such as writing, reporting, and presenting in scientific meetings. Only anonymised, summary level data will be included, and your child will not be identifiable from any information shared.

1. Data ownership
2. Collected data will be stored at World Vision ODK server.
3. Any kind of paper based documents will be stored locked cabinets in the World Vision office.
4. The research findings will be disseminated to the Ugandan authorities, donor organisation, policymakers, scientists, and the general public through a variety of forms such as writing, reporting, and presenting in scientific meetings
5. When authorized staff of VCD requests World Vision to share the data, the collected data will be shared with VCD.
6. Timeline

| **Activity** | **February 2021** | **March**  **2021** | **April**  **2021** | **May**  **2021** | **June**  **2021** | **July**  **2021** | **August**  **2021** | **September 2021** | **October**  **2021** | **November**  **2021** | **December**  **2021** | **January**  **2022** | **February**  **2022** |
| --- | --- | --- | --- | --- | --- | --- | --- | --- | --- | --- | --- | --- | --- |
| IRB preparation |  |  |  |  |  |  |  |  |  |  |  |  |  |
| IRB submission  -1) VCD, 2) UNCST |  |  |  |  |  |  |  |  |  |  |  |  |  |
| IRB pass |  |  |  |  |  |  |  |  |  |  |  |  |  |
| Purchase the materials for prevalence survey and the trial |  |  |  |  |  |  |  |  |  |  |  |  |  |
| Prevalence survey and the trial |  |  |  |  |  |  |  |  |  |  |  |  |  |
| Data aggregation, analysis |  |  |  |  |  |  |  |  |  |  |  |  |  |
| Dissemination the result with stakeholders |  |  |  |  |  |  |  |  |  |  |  |  |  |
| Writing report |  |  |  |  |  |  |  |  |  |  |  |  |  |

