## 2.2 Specific objective

i. To determine the effect of albendazole administration with a fatty meal such as avocado, versus albendazole administration without a fatty meal, on hookworm cure rate and egg reduction rate.

ii. To determine the effectiveness of dual-dose (400mg/day, two consecutive days) versus single-dose (400mg) albendazole treatment regimens on hookworm cure rate and egg reduction rate.

iii. To identify and evaluate environmental, social and cultural variables affecting hookworm infection, and cure rate and egg reduction rate of albendazole against hookworm.

1. Methodology

This study will be embedded within the framework of the MANE project. The baseline prevalence survey was completed in July 2019, and the second prevalence survey is scheduled in September 2021 to evaluate the impact of programs implemented between 2019 and 2021.

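### Two unranked primary outcomes are named, but the trial's aim, 5% error and 80% power are set on cure rate only

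*Protocol*

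**What the plan says.** Section 3.7.1, on the analysis of the trial, states that "the primary outcomes will be cure rate and egg reduction rate among four different groups". The two outcomes stand side by side. No order, split of the error rate or either/both rule is given.

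Section 2.2 asks both treatment questions on both outcomes. Objective i compares giving albendazole with a fatty meal "versus albendazole administration without a fatty meal, on hookworm cure rate and egg reduction rate", and objective ii asks about dose on the same two outcomes.

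Section 3.6.1 (phase II) is narrower. It says that "the aim is to assess the effect of co-administration with fatty foods, and of dual-dose versus single-dose albendazole on hookworm cure rate". The design figures follow for that outcome only: "we power our trial to detect a difference in cure rate of 70% versus 50% for both co-administration with fatty foods versus no co-administration", and likewise for dose. "With type I error probability of 5%, 93 participants in each comparison group will be required for 80% power". From this, "the total target sample size for the trial will be 186", raised to 196 after "allowing for 5% loss to follow-up". No effect size, standard deviation or power is given for egg reduction rate.

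For the tests themselves, section 3.7.1 names a chi-square test of cure rate across the four groups and a paired t-test of egg counts from enrolment to follow-up. It attaches no significance level to either. The p < 0.05 earlier in that section concerns risk factors for infection.

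**The concern.** The protocol's two accounts of what the trial must show do not match. The sample-size section describes a trial with one deciding outcome; the analysis section declares two of equal standing. This has two consequences.

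- Egg reduction rate carries primary status with no stated basis for the trial being large enough to answer it.
- If one outcome favours a regimen and the other does not, nothing fixed in advance says whether that regimen has succeeded. The results are meant to guide the choice of mass treatment strategy, so the deciding outcome should not be open to choice once data are seen.

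Depending on how the gap is later filled, either the false-positive rate per treatment question rises above 5% or the power for overall success falls below 80%.

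**Working it through.** **Inputs from the protocol.** Cure rates 50% and 70%, type I error 5%, power 80%, 93 per comparison group, 186 in total, 5% loss, 196 after loss (section 3.6.1); two primary outcomes (section 3.7.1); both treatment questions asked on both outcomes (section 2.2). Sidedness is not stated. The two-sided reading reproduces the protocol's figure.

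**Step 1: reproduce the sample size.** Two proportions, pooled variance under the null, no continuity correction:

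n = [z(0.975)·√(2·p̄·(1−p̄)) + z(0.80)·√(p1(1−p1) + p2(1−p2))]² / (p1−p2)²

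With p1 = 0.50, p2 = 0.70 and p̄ = 0.60:

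- 1.960 × √0.48 = 1.358
- 0.842 × √0.46 = 0.571
- (1.358 + 0.571)² / 0.04 ≈ 93.0, so 93 per group (power at 93: 80.0%)
- 2 × 93 = 186, and 186 / 0.95 = 195.8, so 196

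All three stated figures are right, and all three are for cure rate.

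**Step 2: if success on either outcome counted.** Assume that both outcomes are compared between the two halves of a factor at 5% two-sided, with no adjustment. The protocol states neither the test level for eggs nor this success rule.

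- Independent test statistics: 1 − 0.95² = 0.0975.
- Correlated test statistics (bivariate normal, chance that at least one |z| exceeds 1.96). The protocol gives no correlation, so a range is shown:

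| Correlation | Chance of at least one false positive, per treatment question |
| --- | --- |
| 0 | 9.75% |
| 0.3 | 9.5% |
| 0.5 | 9.1% |
| 0.7 | 8.3% |
| 0.8 | 7.8% |
| 0.9 | 7.0% |

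The first row is the upper bound under this model. A cured child has a 100% egg reduction by definition, so positive correlation is to be expected and 9.75% is not a central estimate.

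**Step 3: if both outcomes were required.** A false success then needs two false positives, so the error rate stays at or below 5%. Joint power cannot exceed that of the weaker outcome, hence not the 80% for cure rate. It equals 80% only if egg reduction is significant whenever cure rate is, and the protocol gives no basis for assuming that.

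**Step 4: what each remedy does to the sample size.**

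- One primary outcome (cure rate), or a fixed order with cure rate first at 5%: 93, 186 and 196 are unchanged.
- An even split, 2.5% two-sided for each outcome: z(0.9875) = 2.241, so (2.241 × √0.48 + 0.571)² / 0.04 ≈ 112.8, giving 113 per group. That is 226 in total, and 226 / 0.95 = 237.9, so 238. Keeping 93 per group would cut power for cure rate to 71.0%.

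**The case against.** The strongest reply has four parts.

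- **No stated figure is false.** Section 3.6.1 claims 5% for the cure-rate comparison and makes no claim across outcomes. A cure-rate test at 5% keeps its 5% whether or not eggs are analysed as well. This stands.
- **Testing each primary outcome at 5% is only an inference.** A reader might infer that both outcomes will be tested at 5%, so that each treatment question already has two chances of a false positive. The documents do not say so. Section 3.7.1 gives no level for either trial outcome and no either-outcome rule. The only egg test it names for the trial is the paired t-test, which asks whether counts fall after treatment and not whether regimens differ. This also stands, and it makes the figures in step 2 conditional.
- **Error across both factors.** A reader might also multiply the error over fatty meal and dose together. Adjustment across the two factors of a factorial trial is debated, and this point does not rely on it.
- **The statistical analysis plan may settle it.** Error allocation and testing order are commonly left to that plan, which is not shown, so their absence is not a fault in itself. This stands for the procedure but not for the choice of primary outcome, which the protocol fixes here. A later plan that demoted egg reduction rate would contradict section 3.7.1. One that kept both as primary would leave one of them without a sample size in the protocol.

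**Conclusion.** The point holds as a mismatch within the protocol: two unranked primary outcomes in section 3.7.1, against an aim, error rate and power for cure rate alone in section 3.6.1. That rests on the text and needs no assumption.

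The numerical consequence is conditional. The range of about 7% to 10% per treatment question requires a between-arm egg test, 5% two-sided on each outcome, success on either, and correlations from 0 to 0.9. Under a both-outcomes rule there is no inflation, and the cost falls on power instead.

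The documents do not support the stronger conclusion that the plan already exceeds its stated 5%. The sample-size arithmetic is correct. This is a cheap improvement.

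**What to change.** In section 3.7.1, name cure rate at day 21 as the single primary outcome for each of the two factors, since that is the outcome the trial is sized on. Make egg reduction rate the key secondary outcome, or test it in fixed order only after cure rate has succeeded for that factor. In either case, name a between-arm comparison for it, because the paired t-test does not answer objectives i and ii. Align the wording of section 2.2 if needed.

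The cost is about one sentence. The targets of 93, 186 and 196 do not change, whereas an even split of the error rate would need 238 children. The small downside is that a positive egg reduction result alone would no longer count as a primary success.
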